### Blinding

Functional outcome examiners are blinded to participant treatment assignment. The physical nature of the treatments prevents blinding of participants and providers to treatment assignment.

### Interventions

Participants receive both SMT and SRE for either 12 weeks or 36 weeks. All are requested to abstain from seeking treatment for their back or neck outside the study. Treatment protocols are based on previous studies by the investigators [[40]] and study clinicians input. The approach to treatment is pragmatic in nature intended to reflect real-world, patient-centered practice and is tailored to participants’ age, physical condition, and preferences [[23]]. Standardized forms are used to document treatment procedures, adverse events, and participant compliance; all forms are reviewed daily for completeness and protocol compliance. See Table 2 for descriptions of the interventions.

**Table 2 T2:** Descriptions of the interventions

**Intervention**	**Type**	**Program design**	**Delivery method**	**Dose**
SMT	High velocity, low amplitude manipulation (can be drop-table assisted) [[41]]	Individualized: spinal regions treated and type of therapy used is determined by the chiropractor [[42],[43]]	Treatment delivered by licensed chiropractors with at least 5 years experience	20 to 30 minute visits
				Minimum: 1 visit/month
	Low velocity, low amplitude mobilization			Maximum: 2 visits/week
				Individualized: Number of treatments determined by chiropractor & patient [[40],[44],[45]]
	Manual distraction, gentle soft tissue massage, hot or cold therapy, and active or passive muscle stretching to facilitate SMT			
SRE	Aerobic warm up	Partially individualized: exercise selection, progression, and repetitions are determined by patient’s abilities and tolerance	Supervised by exercise therapists*	45 to 60 minute sessions
	Stretching, strengthening, and balance exercises			
				Minimum: 1 session/month
			One-on-one	
				Home exercise encouraged between sessions
	Advice to stay active; self-care tips for pain management [[46],[47]]		Uses resistance bands, stability trainers, chairs	

*Exercise therapists are under the supervision of treating chiropractors.

### Spinal manipulative therapy (SMT)

SMT and mobilization are defined as the application of manual force to the spinal joints. Each SMT appointment is approximately 20 to 30 minutes and includes history, examination, and treatment. Appointments focus on complaints of the cervical and lumbar spine; however, other musculoskeletal complaints may be addressed if it impacts spine-related disability (e.g., hip complaint can be addressed if it impacts low back). Treatment areas are identified by palpatory spine tenderness [[42]], decreased vertebral motion, abnormal joint play, or abnormal end feel determined by passive motion tests [[43]]. Treatment procedures include high velocity low amplitude thrust, which can be drop-table assisted [[41]], and low velocity low amplitude mobilization. Manual distraction, gentle soft tissue massage, hot or cold therapy, and active or passive muscle stretching can be used to facilitate or as an adjunct to SMT.

### Frequency of SMT treatment

The minimum frequency of SMT appointments is one per month with a maximum of two per week. The number and frequency of appointments are determined by the chiropractor and patient, guided by responses to a modified version of the Measure Yourself Medical Outcome Profile [[44],[45]].

### Supervised rehabilitative exercise (SRE)

Exercise therapy is defined as progressive stretching, strengthening, and balance exercises, which use resistance bands and stability trainers. SRE sessions are delivered by exercise therapists, under the supervision of chiropractors, in individual 45 to 60 minute sessions. There are 4 sessions spaced throughout the 12 week intervention and 10 sessions in the 36 week intervention. Exercises focus on increasing spinal mobility, strengthening supporting spinal musculature, and increasing overall stability and proprioception (see Table 3). All sessions include a 5 to 10 minute aerobic warm up on a treadmill or stationary bike. At the first session, participants are given information about their spine-related condition, self-care tips for pain management, and benefits of exercise for back and neck problems. Participants review goals of the SRE program and set personal activity goals with their therapist. During the second session, strengthening exercises and body mechanics for activities of daily living are introduced. Exercises are introduced at an intensity commensurate to the participant’s level of fitness and abilities based upon the therapist’s assessment. Subsequent sessions review previous exercises and check for proper form. Ongoing encouragement to promote physical activity and movement to decrease fear avoidance is provided [[46],[47]].

**Table 3 T3:** Details of exercises in SRE program

**Type (Freq)**	**Exercise**	**Sets**	**Repetitions**	**Exercise description**	**Progressions**
Stretching (performed daily at home)					
	head retraction	1	5	Seated with head in neutral position, alternate retracting head back and returning to neutral.	
	cat camel	1	5	Begin with the pelvis in a neutral position, alternate between arching the back in a “C” shape forward and backward.	1: Seated
					2: Hands/knees
	shoulder shrug	1	1	Seated with head and neck in neutral position, raise shoulders in a cephalic direction, and release.	
	neck forward bend	1	1	Seated with head in neutral position, flex head forward to bring chin toward the chest.	
	neck side bend	1	1	Seated with head in neutral position, keep shoulders stationary, tip head to side approximating ear to shoulder. Release & repeat on other side.	
	hamstring stretch	1	1	Seated with one leg straight and one leg bent, flex at the waist while keeping leg straight. Repeat on other side.	
	seated hip stretch	1	1	Seated, place one ankle on the opposite knee. Use the hand to add pressure on bent knee to externally rotate the hip. Repeat on other side.	
Balance (performed daily at home)					
	knee lift	up to 2	up to 5	Stand next to a chair; bend one knee to lift the foot a few inches off the floor; slowly lower foot to floor. Repeat on other side.	1: Chair assisted
					2: Stability trainer, chair assisted
					3: Unassisted
					4: Stability trainer, unassisted
	stance/lunge	up to 2	up to 5	Stance: Stand with feet together, step forward so heel touches the opposite foot’s toes. Return to the start position; repeat on other side.	1: Semi-tandem stance, chair assisted
					2: Semi-tandem stance, unassisted
					3: Stability trainer, semi-tandem stance, chair assisted
					4: Stability trainer, semi-tandem stance, unassisted
					5: Semi-tandem lunge, chair assisted
					6: Stability trainer, semi-tandem lunge, chair assisted
					7: Tandem stance, chair assisted*
					8: Tandem stance, unassisted*
					9: Stability trainer, tandem stance, chair assisted*
					10: Stability trainer, tandem stance, unassisted*
				Lunge: Begin with feet together, take an exaggerated step forward. Lower the knee of the back leg towards the ground and then rise to return to starting position with the feet together. Repeat on other side.	
Strengthening (performed every other day at home)					
	bird dog	up to 2	up to 5	Begin on hands and knees, extend either one or two (contra lateral) extremities parallel to floor. Return to start position; repeat on other side.	1: Hands/knees leg only
					2: Hands/knees, leg and arm combined
					3: Stability trainer, hands/knees, leg and arm combined
	push up	up to 2	up to 10	From a plank position, lower the body by bending the arms, keeping the back straight. Return to start position.	1: Wall
					2: Kneeling
					3: Full body
	abdominal curl	up to 2	up to 10	Lie face up on floor with one knee bent and one leg straight; lift the shoulders off the ground and flex at the waist; release. After first set, switch bent knee.	1: Supine on floor, hands at side
					2: Supine on floor, arms on chest
					3: Supine on floor, hands behind head
					4: Supine on floor, hands overhead
					5: Stability
					trainer, hands at side
					6: Stability trainer, arms on chest
					7: Stability trainer, hands behind head
					8: Stability trainer hands overhead
	resisted head retraction	up to 2	up to 10	Seated with head in neutral position facing a closed door. A resistance band is looped around the head/forehead with end secured by a firmly closed door. Alternate head retraction and release.	1: Yellow Theraband®
					2: Red Theraband®
					3: Green Theraband®
	chair squat	up to 2	up to 10	Stand in front of a chair, bend knees and hips to lower body to a seated position; return to standing.	1: Two handed assist
					2: Arms at sides
					3: Arms crossed
					4: Arms out front
					5: Stability trainer, arms at sides
					6: Stability trainer, arms crossed
					7: Stability trainer, arms out front

*Only one set is required to progress.

Sets and repetitions listed are for each side, if appropriate. Progressions are introduced when the participant can complete the maximum number of sets and repetitions with proper form. Neutral position of the head implies a relaxed posture, the ears aligned with the shoulders. Neutral pelvis cues the patient to position themselves with a slight, not exaggerated, lordosis in the lumbar spine.

Participants are encouraged to perform the exercises at home between supervised sessions (see Table 3). To encourage compliance with home exercise, exercise logs, resistance bands, stability trainers, and exercise handouts are provided. The handouts feature pictures of older adults performing the exercise with simple written instructions.

### Compliance

To be considered compliant in the 36 week group, participants must attend one SMT appointment per month for eight of the nine months and eight of ten SRE sessions. Compliance in the 12 week group is defined as attending one SMT appointment per month for all three months and three of four SRE sessions.

### Rescue medication & reasons for withdrawal

For individuals experiencing acute exacerbation of pain, rescue medications are available by prescription from a study medical doctor following an evidence-based protocol. If a participant becomes involved with litigation for a neck- or back-related condition, demonstrates progressive neurological signs, or develops any co-morbidity that increases the risk of study participation (e.g., a new transient ischemic attack), they are withdrawn from treatment by the steering committee. Participants with medical conditions that warrant additional follow up and treatment are referred.

### Data collection

Outcome measures are collected through self-report questionnaires, interviews, and blinded functional assessments (see Table 4 for data collection schedule). Patient flow characteristics (i.e., number evaluated, disqualified, etc.) are monitored according to the Consolidated Standards of Reporting Trials (CONSORT) guidelines for standardized reporting of clinical trials [[48]].

**Table 4 T4:** Data collection schedule

	**BEV1**	**BEV2**	**W4**	**W12**	**W24**	**W36**	**W37**	**W52**	**W78**
**Demographics**	**X**								
**Clinical characteristics/physical examination**	**X**								
**Self-report outcome measures**									
Disability: NDI [[49]] and ODI [[50]]	**X**	**X**	**X**	**X**	**X**	**X**		**X**	**X**
Pain: 11-box scale [[51]]	**X**	**X**	**X**	**X**	**X**	**X**		**X**	**X**
General health: EuroQol EQ-5D [[52]]	**X**	**X**	**X**	**X**	**X**	**X**		**X**	**X**
Improvement [[40],[53],[54]]			**X**	**X**	**X**	**X**		**X**	**X**
Pain Self-Efficacy Questionnaire [[55]]	**X**	**X**	**X**	**X**	**X**	**X**		**X**	**X**
Tampa Scale for Kinesiophobia [[56],[57]]	**X**	**X**	**X**	**X**	**X**	**X**		**X**	**X**
Satisfaction [[40],[53],[54]]			**X**	**X**	**X**	**X**		**X**	**X**
Medication use [[40],[53]]	**X**	**X**	**X**	**X**	**X**	**X**		**X**	**X**
Expectations [[40],[53]]		**X**		**X**	**X**	**X**		**X**	
Falls [[58]]		**X**		**X**	**X**	**X**		**X**	**X**
*Side effects [[40],[59]]			**X**	**X**	**X**	**X**			
Home exercise frequency			**X**	**X**	**X**	**X**		**X**	**X**
Self-reported influence	**X**	**X**	**X**	**X**	**X**	**X**		**X**	**X**
**Functional outcome measures**									
Hand grip strength [[60]]		**X**					**X**		
Short physical performance battery (SPPB) [[61],[62]]		**X**					**X**		
Accelerometry (7 days) [[63]]		**X**				**X**			
**Qualitative data collection**									
Interviews				**X 12wk**		**X 36wk**			

BEV = Baseline evaluation; W = weeks post-randomization; 12wk = 12 week treatment group only; 36wk = 36 week treatment group only.

*Also collected at treatment visits during intervention phase: BL2-W12 for 12wk group; BL2-W36 for 36wk group.

### Primary outcome measures

#### Self-report questionnaires

##### Back and neck disability

The Oswestry Disability Index [[50],[64]] (ODI) version 2.0 (section 4, item 6, has been modified to read “I am in bed most of the time.”) and the Neck Disability Index [[49]] (NDI) are valid and reliable outcome measures for back- and neck-related disability. The NDI was derived from the ODI; therefore, both instruments have similar measurement properties, which may aid in the comparison of results. Each outcome measure has 10 sections, each section with six possible responses that reflect increasing disability (0 = no disability, 5 = maximal disability).

### Secondary outcome measures

#### Self-report questionnaires

##### Pain

Patients with spinal conditions consider pain to be one of the most important outcome measures [[65]]. Participants are asked to rate their typical level of neck, mid back, arm, low back, and leg pain during the past week on an 11-box scale (0 = no pain, 10 = worst pain possible); one response for each area [[51]].

##### General Health

The EuroQol EQ-5D [[52]] is used to determine the participant’s general health state. It is a multi-attribute utility scale that measures five dimensions (mobility, self-care, usual activities, pain/discomfort, anxiety/depression) with three response levels (no problem, moderate problem, severe problem). It also includes a visual analog scale, the EuroQol thermometer, which measures overall health status.

##### Improvement

Improvement in both back and neck problems after starting treatment in the study is measured using a single nine-point ordinal scale (1 = no symptoms/100% improvement, 9 = as bad as it could be/100% worse) [[40],[53],[54]].

##### Self-efficacy

The Pain Self-Efficacy Questionnaire is a valid and reliable [[55]] 10-item scale used to assess the participant’s confidence level (0 = not at all confident, 6 = completely confident) when performing physical and social activities in the presence of chronic pain.

##### Kinesiophobia

The Tampa Scale of Kinesiophobia [[56],[57]] measures fear of movement and (re)injury; it has been shown to be valid and reliable in chronic pain conditions [[66]] including back pain [[67]]. It is a 17-item tool that is scored using a four-point Likert scale (1 = strongly disagree, 4 = strongly agree).

##### Satisfaction

Participants will rate how satisfied they are with the care they have received in the study on a seven-point scale (1 = completely satisfied/couldn’t be better, 7 = completely dissatisfied, couldn’t be worse) [[40],[53],[54]].

##### Medication Use

Participants report frequency of use for over-the-counter and prescription medications for their back or neck problem during the past week; this is measured using an eight-point scale (0 = have not taken any, 7 = every day). Participants then identify the medications used during the past week [[40],[53]].

Improvement, satisfaction, and medication use outcome measures have not been tested for validity or reliability.

### Functional outcome measures

Functional outcome assessments take approximately 30 minutes and occur at baseline and week 37.

#### Functional ability

##### Hand Grip Strength

Hand grip strength, a surrogate of overall functional ability and mortality [[68]–[70]], measures the grip strength exerted in a maximum effort using a hand-held hydraulic dynamometer (JAMAR Hand Dynamometer, Therapeutic Equipment Corporation, Clifton, NH) [[71],[72]]. The procedure and scoring rubric are from Mathiowetz et al. [[60]]. This test was modified by alternating hands between each measurement; further, it is considered invalid if the participant cannot perform 3 or more contractions or if there is more than a 20 kg difference between any two measurements.

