##### Short Physical Performance Battery (SPPB)

The SPPB is shown to predict future disability in healthy community dwelling older adults over the age of 70 [[62]]. Adapted from the National Institute on Aging, it is comprised of three tests: gait speed, standing balance, and chair rising [[61]]. Each component of the SPPB is scored on a five-point scale (0 = inability to perform, 4 = highest level of performance); these are summed to produce a composite score. The protocols and scoring rubrics are based on the method developed by Guralnik et al. [[62]].

Modifications of the SPPB include reordering of the tests and performing tests on a force plate. Specifically, gait speed is performed first with the shoes on, while the two remaining components are completed in stocking feet on the force plate. The force plate records ground reaction forces during the standing balance and chair stand tests (Bertec Force Plate, Model #4060-NC, Bertec, Inc, Columbus, OH) using Motion Monitor data acquisition software (Innovative Sports Training, Inc, Chicago, IL) to define the participant’s center-of-pressure.

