### Data analysis

#### Statistical methods

Data analyses will be conducted using SAS for Windows (Release 9.1 or higher). Descriptive statistics will be calculated to describe patient baseline characteristics in each treatment group and to assess comparability and generalizability. Baseline values of self-report outcome variables will be obtained by averaging the two baseline visits. Demographic and clinical variables determined by the investigators to impact outcomes or those that have a correlation of 0.5 or greater will be considered as other possible covariates [[78]]. Intention-to-treat analysis will be used; patients with one or more follow up measures will be included in the analysis. Normality assumptions will be evaluated through normal probability plots and data transformed, if necessary.

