### Primary and secondary analyses

Primary analysis will use a linear mixed-model method for repeated data to test for between-group differences in neck and back disability separately at week 36, with baseline variables that may influence outcomes as covariates [[82],[83]]. Secondary analysis of disability will include testing for between-group differences at weeks 4, 12, 24, 52, and 78, as well as within-group change at all time points. Longitudinal analysis will be performed through the short (weeks 4, 12, 24 and 36) and long term (weeks 4, 12, 24, 36, 52 and 78).

Secondary outcome measures, including pain, general health, improvement, self-efficacy, kinesiophobia, satisfaction, medication use, and functional outcome measures will be similarly calculated for within- and between-group differences. This study is not powered to detect change in the secondary outcome measures.

Content analysis of qualitative interviews will use both inductive and deductive approaches [[84]] to identify themes that occur in response to questions asked [[85]]. When coding is complete, frequency of themes will be quantified and representative quotations will be identified [[85],[86]].

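### As worded, the hand grip validity rule can void a test for a true right–left difference or for inability to complete it, which makes loss of a week 37 value depend on the outcome

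*Protocol article*

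**What the plan says.** Under Hand Grip Strength, the protocol article presents the measure as a proxy for function: "Hand grip strength, a surrogate of overall functional ability and mortality". It takes the method from a cited source ("The procedure and scoring rubric are from" a publication that is not shown) and then adds its own specification. First: "This test was modified by alternating hands between each measurement". Second, a test will be "considered invalid if the participant cannot perform 3 or more contractions or if there is more than a 20 kg difference between any two measurements".

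Under Short Physical Performance Battery, each component has a five-point scale: "0 = inability to perform, 4 = highest level of performance".

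On timing: "Functional outcome assessments take approximately 30 minutes and occur at baseline and week 37". The data collection schedule (Table 4) shows no other grip assessment. Secondary aim 2 compares the groups on functional outcomes at week 37. Additional aim B looks at within-group change at that visit in the exercise-alone group (n = 18).

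On analysis: "Intention-to-treat analysis will be used; patients with one or more follow up measures will be included in the analysis". On the standing of these outcomes: "This study is not powered to detect change in the secondary outcome measures".

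**The concern.** The rule has two limbs, and each can remove a real result.

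- **Contractions.** A participant who cannot complete three contractions at week 37, whether from pain, weakness or another physical cause, has the test declared invalid. On a measure of function, that inability is information about the outcome.
- **The 20 kg limit.** It applies to any pair of readings while the hands alternate, so a right-hand reading may be set against a left-hand one. A participant with one good and one impaired hand can then be voided for a true difference. One-sided arm or hand trouble is plausible here: every participant has neck disability, arm pain is a secondary outcome, and arm or hand numbness is a listed side effect.

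If an invalid test yields no value, loss at week 37 depends on the participant's own week 37 performance. No intermediate or later grip value can inform the model. An imbalance between arms in such losses would bias the aim 2 comparison.

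**Working it through.** The documents contain no figure for invalid grip tests, so there is nothing of the plan's own to reproduce. The wording can be compared directly. Every size below rests on stated assumptions.

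**Step 1. Two measures at the same visit**

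| | Grip | SPPB |
|---|---|---|
| Participant cannot perform | Test invalid | Component scored 0 |
| Result kept as poor function | Not stated | Yes |

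The contraction limit also leaves open whether three means per hand or in total. With alternating hands, three in total means two readings from one hand and one from the other.

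**Step 2. What the 20 kg limit can catch within one hand**

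Assume independent normal trial error with SD s in one hand. For two trials, P(|difference| > 20) = 2 × [1 − Φ(20 / (s√2))].

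- s = 2 kg: 20 / 2.83 = 7.07, P = 1.5 × 10⁻¹²
- s = 3 kg: 20 / 4.24 = 4.71, P = 2.4 × 10⁻⁶
- s = 4 kg: 20 / 5.66 = 3.54, P = 4.1 × 10⁻⁴

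On these assumptions, a same-hand check at 20 kg hardly ever triggers. When the rule does trigger, it is almost always across hands.

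**Step 3. Whom the 20 kg limit removes**

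Readings cannot be negative, so a gap above 20 kg requires at least one reading above 20 kg. A participant whose readings are all 20 kg or less can never be voided by this limb.

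An illustrative simulation assumed mean grip 22 to 38 kg, SD 5 to 9 kg, between-hand correlation 0.8 to 0.9, trial error 1.5 to 3 kg and three trials per hand.

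- Literal any-two rule: about 0% to 2.3% of tests voided, i.e. at most about 2 in an arm of 100.
- Same-hand rule: at most 0.002% voided.
- In one scenario (mean 30 kg, SD 9, correlation 0.8, error 3 kg), voided tests averaged 30.2 kg against 30.0 kg overall. The better hand averaged 37.8 kg against 32.5 kg.
- In the scenarios where any test was voided, 9% to 12% of voided tests fell in the lowest decile, close to the 10% expected if voiding were unrelated to overall grip.

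The simulation does not model one-sided impairment, which would raise the voided share.

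**Step 4. What the contraction limit could do**

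Assume mean grip of 25 kg in those who complete the test and 8 kg in those who cannot, with a proportion p voided. The true arm mean is 25(1 − p) + 8p, and the mean of those kept is 25. The upward shift within one arm is therefore 17p.

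| p | True mean (kg) | Shift in one arm (kg) |
|---|---|---|
| 0.03 | 24.49 | 0.51 |
| 0.05 | 24.15 | 0.85 |
| 0.10 | 23.30 | 1.70 |

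Aim 2 is a difference between arms, so the relevant bias is 17 × (p₁ − p₂):

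- equal voiding: 0 kg
- 5% against 3%: 17 × 0.02 = 0.34 kg
- 10% against 3%: 17 × 0.07 = 1.19 kg

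The bias favours the arm with more inability. In the exercise-alone group there is no comparator to cancel the shift, and one voided test is 1/18 = 5.6% of the group.

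**The case against.** A reader might infer that the rule as a whole strips the functional outcome of its worst results. The documents do not support that. Step 3 shows that the 20 kg limb selects asymmetry and cannot touch participants with uniformly low readings. The contraction limb sets no minimum force, so a very weak participant who squeezes three times stays in the data. The text speaks of inability to perform, not of weakness.

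A reader might also take 0.5 to 1.7 kg as the bias in the treatment comparison. Those are shifts within a single arm under assumed inputs, and equal voiding cancels. The eligibility criteria (community dwelling, ambulatory, no stroke, no progressive neurological deficit) give no reason to expect 3% to 10% of participants to be unable to squeeze three times. Functional examiners are blinded, so the validity call does not depend on knowing the arm.

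Two further points have weight. A same-hand consistency check may have been intended. The article also does not say whether an invalid test is repeated, scored low or set to missing; the cited rubric or a fuller plan may settle this, and its absence from an article is no fault.

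These points limit the size and reach of the concern. What stands is the stated rule: it is presented as the trial's own specification, it covers any pair of readings under alternating hands, and it classes inability as invalid. Blinding prevents a deliberate imbalance but not one that arises because the arms differ in function.

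**Conclusion.** The point holds as a minor defect in a stated scoring rule. As worded, the 20 kg limit can void a grip test for true asymmetry, and the three-contraction limit can void it for inability, which the SPPB treats as a result. With one follow-up, any week 37 value dropped in this way is lost to aim 2 for a reason tied to the outcome.

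The size cannot be derived from the documents. On the assumed inputs the literal 20 kg rule voids at most about 2.3% of tests (more if one-sided impairment is common), and modest differential voiding for inability moves the arm difference by a few tenths of a kilogram. That values are actually lost is an inference from the ordinary meaning of invalid. Grip is one of three functional measures and is secondary and unpowered; the primary Oswestry and Neck Disability Index analyses are unaffected.

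**What to change.** 1. Apply the 20 kg check only between trials of the same hand. When it is exceeded, flag or repeat the trial and do not void the test.
2. Keep and analyse the contractions that were recorded, and record the reason for any inability. State whether the required three are per hand or in total.
3. Report the number of invalid tests by arm, at baseline and at week 37, with the limb of the rule that was met.
4. Add a sensitivity analysis that gives the lowest rank to participants physically unable to perform. This is better than entering 0 kg in the main analysis: grip is a continuous force, and 0 kg would be a value that nobody measured.

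For tests already done, repetition is no longer possible, but they can be re-scored if the individual readings were kept. The trial timeline places cleaning and analysis after data collection, in 2015, which leaves room to do so. The cost is a scoring note, some re-scoring work and slightly noisier values where a participant contributes fewer trials.
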